### Data monitoring

An interim analysis of the data collected at the 3 months’ follow-up will be done to assess progress in the outcome measures in response to the delivery of the interventions. Due to the non-invasive nature of the interventions, no stopping rules will be made to terminate the study and emphasis will be made that participants are free to withdraw from the study if the interventions become unacceptable. No Data Monitoring Committee is available in the researcher’s institution and therefore no external body outside the study team will be monitoring the data.

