*Motivational interviewing*: A single 30–45-min MI session will be offered by one researcher (MI) experienced in motivational interviewing for promoting oral health care. This component will target the perceived control construct of the TPB. The researcher providing the MI will receive training using the MI network of trainers’ resources [24]. The MI session includes establishing rapport and encouraging participants to talk about their dental habits and what they want for their children to motivate them to accept changes in behaviors. Options and strategies for improving dental health will be discussed. After the session, parents will be contacted by phone every 2 months, for 6 months, to reinforce commitment to the new behavior and provide support. Without follow-up, new behaviors may not be maintained or even tried leading to relapse.

*Oral health promotion messages*: Teledentistry and mobile health (mHealth) are proving to be an effective tool for the promotion of oral health in various age groups [25]. mHealth components will be incorporated in the proposed study to reduce the time needed for parents to receive health education, adhere to physical distancing in the time of COVID-19, and make use of the popularity of these tools among the younger generations. A series of unique messages targeting the subjective norms construct of the TBP will be developed by the researchers (MI, MET, and WE) and sent to the parents using the WhatsApp Messenger [26]. The messages are based on previous studies [23, 27] and are modified to fit the proposed study. The validity, acceptability, preferred frequency, and timing of messages will be determined in the feasibility pilot study of the preparation phase (Appendix 1). Based on the frequency, the number of messages will be determined so that they are spread over the study period.

The following are examples of the messages:

“{name}, this is {dentist} from {clinic}. Did you know that brushing your children’s teeth twice daily using a toothbrush and toothpaste will help them have a nicer smile in front of their friends and family?”

“{name}, this is {dentist} from {clinic}. Ensure smaller dental bills for your family by brushing your child’s teeth twice daily using a toothbrush and toothpaste.”

“{name}, this is {dentist} from {clinic}. Be a role model for your children and show them how to brush their teeth twice daily using a toothbrush and toothpaste”.

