1. Primary outcome: Reduction in the dental plaque index scores of children of participating parents after 3 and 6 months [31] will be measured using the modified plaque index (PlI) of Silness and Löe [32] by another researcher than the one providing the intervention (NA). The World Health Organization (WHO) community periodontal index of treatment needs (CPITN) probe and a disposable dental mirror will be used to assess plaque on 6 index teeth (upper right 2nd primary molar, upper primary right lateral incisor, upper left 1st primary molar, lower left 2nd primary molar, lower left primary lateral incisor, and lower right 1st primary molar) at baseline and after 3 and 6 months. The four surfaces of each tooth will be scored from 0 to 3 and the scores will be averaged per tooth. The scores of the six teeth will be averaged to obtain the mean PlI of the child. The outcome measure is the percent reduction in dental plaque scores calculated as: [(plaque score after 3 or 6 months − plaque score at baseline)/ plaque score at baseline] × 100. The primary outcome measure is reduction in plaque index scores after 6 months.

2. Secondary outcome: Parent-reported frequency of brushing the child’s teeth using fluoridated toothpaste will be assessed by the Arabic version of the WHO questionnaire [33] at baseline, after 3, and 6 months. The questionnaire assesses the frequency of toothbrushing on a 7-point scale ranging from never to twice or more a day. The outcome measure is the change in frequency from baseline to 3 or 6 months categorized as increased (changing from lower to higher frequency), remained the same (reporting the same frequency) and decreased (changing from higher to lower frequency). (Appendix 2)

3. Moderators such as child’s age and sex, the number of children in the family, parents’ age, oral hygiene practices, and education level will be assessed by the questionnaire.

*Participant timeline*: Participant timeline is shown in Fig. 2.

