### Trial status

This is the original version of the protocol, issued on the 9th of June 2021. The recruitment is planned to start on the 20th of August 2021 and end approximately by February 2022. Any changes or protocol amendments will be made to the study record available on clinical trials.gov.

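### The study team plans to analyse 3-month outcomes with no stated decision attached, while delivery and the 6-month assessments are still running

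*Protocol article*

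**What the plan says.** All references are to the protocol article.

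- **Purpose of the look (Data monitoring).** The 3-month data will be analysed as an interim analysis, which "will be done to assess progress in the outcome measures in response to the delivery of the interventions".
- **Decision attached (Data monitoring).** The section states that "no stopping rules will be made to terminate the study". It names no other use, such as a sample-size review or a change to a component.
- **Who sees the data (Data monitoring).** The institution has no monitoring committee, and "no external body outside the study team will be monitoring the data".
- **Primary endpoint (Factorial trial design, outcome measures).** "The primary outcome measure is reduction in plaque index scores after 6 months".
- **Delivery after month 3 (Identifying candidate components).** In the motivational interviewing component, "parents will be contacted by phone every 2 months, for 6 months, to reinforce commitment to the new behavior and provide support". The WhatsApp messages are also to run for the length of the study.
- **Calendar (Trial status).** "The recruitment is planned to start on the 20th of August 2021 and end approximately by February 2022".
- **Blinding (Randomization and allocation concealment).** The plaque examiner and the two researchers analysing the data are to be blinded to allocation. The label of one of those analysts is the same as that of the researcher who gives the interviewing session.

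**The concern.** An interim analysis usually serves a decision, such as stopping, adapting, resizing or protecting participants, and that decision justifies the risk of showing emerging results to people who can still influence the trial. Here the only stated purpose is to see progress, and the people who see it belong to the team that is still running the trial.

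The risk is operational bias. Someone who knows that one component looks strong or weak at 3 months may put more or less effort into later support calls, or pursue retention unevenly. They may also convey expectations to parents, whose reported brushing frequency is the secondary outcome, or let the early result shape later analysis choices. Under the section on selecting components, each component is kept or dropped according to whether its main effect reaches a moderate size. A modest shift could therefore change which components enter the optimized package.

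**Working it through.** **1. The plan's own figure.** The sample size calculation uses partial eta squared 0.06, so f = √(0.06/0.94) = 0.2526. With numerator df 1, denominator df N − 8, noncentrality f²N, alpha 0.05 and power 80%, the smallest N is 126 (power 0.803). At the planned 160, power is 0.888. No alpha is set aside for the interim, and none is needed for the 6-month test if the trial cannot stop early. The fix below leaves these figures unchanged.

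**2. Is the trial still running at the look?** Recruitment from 20 August 2021 to about February 2022 is roughly 6 months. A complete 3-month data set would exist around May 2022, and the last 6-month visits would fall around August 2022. The protocol gives no date for the interim.

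**3. Exposure.** Assume uniform accrual of 160 parents over months 0 to 6. For a look at trial month t (between 6 and 12), parents enrolled after month t − 6 have not reached 6 months:

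outstanding = 160 × (12 − t)/6

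| Look at month | 6-month outcomes outstanding |
|---|---|
| 8 | 160 × 4/6 ≈ 107 |
| 9 (last parent reaches 3 months) | 160 × 3/6 = 80 |
| 10 | 160 × 2/6 ≈ 53 |
| 12 | 0 |

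**4. Calls still to be made.** Conditions 5 to 8 of Table 2 include interviewing: 4 × 20 = 80 parents. Calls every 2 months fall at about months 2, 4 and 6 for each parent. At a month-9 look under the same assumptions, parents enrolled after month 3 (80 × 3/6 = 40) still await the month-6 call. Those enrolled after month 5 (80 × 1/6 ≈ 13) also await the month-4 call.

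**5. Type I error.** With no stopping, the 6-month test read alone stays at 5%. Only if both the 3-month and 6-month results were read at 5% as evidence would the chance of at least one false positive per component rise. It would then be 0.095 to 0.070 for assumed correlations of 0.3 to 0.9 between the two estimates. The protocol names 6 months as primary, so this is not the point made here.

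**6. What an operational drift would do (sizes assumed).** A main effect compares 80 with 80, so its standard error is √(1/80 + 1/80) = 2/√160 = 0.158 SD. For a drift of b SD toward one component, δ = b/0.158, and the false-positive rate is 1 − Φ(1.96 − δ) + Φ(−1.96 − δ).

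| Assumed drift b (SD) | δ | False-positive rate |
|---|---|---|
| 0.05 | 0.316 | 0.062 |
| 0.10 | 0.632 | 0.097 |
| 0.20 | 1.265 | 0.244 |

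Nothing in the protocol indicates which drift, if any, would occur.

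**The case against.** Much of the case on the other side stands.

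- **The primary outcome assessor.** A reader might infer that interim results reach the person scoring plaque. The protocol does not support this. The examiner is separate from the intervention provider, is to be blinded, and is not one of the two listed analysts.
- **Loss of blinding.** A reader might infer that the look unblinds the investigators. Group means do not reveal any one child's allocation, and the interviewing researcher already knows who received interviewing from delivering it. That overlap of roles would exist without an interim.
- **Who does what.** The protocol names neither the person who runs the interim nor the person who makes the support calls. The overlap between interviewer and analyst rests on a shared label, so it is an apparent overlap.
- **By condition.** The wording would also fit a pooled before-and-after check. A response to the interventions is more naturally read as a comparison of conditions, but that remains an inference.
- **Narrow routes.** Messages and videos are prepared material with a frequency set from the pilot, and the last call falls close to the endpoint. The protocol also commits to seeking outcome data from participants who discontinue.
- **Condensed article.** The full protocol is a supplement that is not shown, and it may restrict access to interim results.

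These points narrow the concern but do not remove it. The article itself commits to the look, gives its purpose, attaches no decision and rules out outside monitoring. That is a stated plan and not an omitted detail.

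**Conclusion.** The concern holds in a limited form. The plan has the study team look at 3-month outcomes, most naturally by condition, with no stated decision that uses the result, while delivery and primary outcome collection continue. Comparative results may reach someone involved in delivery.

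The figure of about 80 of 160 outstanding outcomes rests on two assumptions: uniform accrual over 6 months and a look when the last parent reaches 3 months. An earlier look leaves more outstanding and a later one fewer. It shows how much of the trial is exposed, not how large a bias would be, and the latter cannot be derived from the document.

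Two further stronger readings should be avoided. The look does not inflate the type I error of the 6-month test. Nor does the text show that the analysis has no benefit, only that no decision is stated for it. The point is worth correcting because the remedy is cheap; it does not invalidate the design.

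**What to change.** Amend the Data monitoring section to say that the 3-month analysis by condition will be run only after the last 6-month visit and data lock. Until then, the team reviews only data pooled over all conditions: attendance, completeness, withdrawals and reported adverse events. If a pooled review is what was meant all along, one sentence saying so settles the matter.

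The cost is a sentence or two of text and the loss of an early view of 3-month effects that no stated decision uses. The sample size of 160, the 5% level and the power of 0.888 do not change.

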### Harms

Participants will be contacted by phone every 2 months, for the duration of the trial to assess reported adverse events or any other unintended effects. This will also be assessed at the 3 months’ follow-up appointment.

### Auditing

No auditing is planned or expected.

### Ethics approval and consent to participate

The study received approval from the Ethics Committee of the Faculty of Dentistry, Alexandria University. IRB No: 00010556-IORG: 0008839. A signed informed consent will be obtained by the principal investigator (MI) from each parent. The informed consent that will be signed by the parents will encompass the data to be collected and its intended analysis and use for the study purpose. No additional studies are planned, and no biological samples are to be collected because of the focus of the study on parents’ behavior and its impact on plaque accumulation in children. The voluntary nature of the study will also be emphasized in the consent form, and the parents will be informed of their right to withdraw from the trial anytime, without incurring any penalties. In addition, no advice will be given to the participants to avoid receiving or seeking any health education content.

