*Randomization and allocation concealment*: Parents will be assessed for eligibility and randomly allocated by the Ralloc Stata Software [36] to the 8 experimental conditions (Table 2) using a permuted block of size 16, to be able to balance the sample size across the randomization groups. Each block will be a list of 8 randomly ordered conditions, and participants will be randomized to the condition listed in the permuted block. Once all allocations in a block have been used, the next permuted block will be utilized. The randomization schedule will be kept in opaque, sealed envelopes, and the envelopes will be arranged sequentially by a dental assistant who will not be involved in the study. Each envelope will be opened after completing the child’s oral examination at baseline and the experimental condition to which the parent is allocated will be administered. Parents’ enrollment, random sequence generation, and allocation to experimental conditions will be done by an independent researcher (RY) who will be different from the researcher implementing the experimental conditions and assessing the outcomes. The researcher also clinically assessing plaque accumulation (primary outcome) (NA) and the researchers involved in data analysis (MI, MT) will be blinded to the assignment to interventions. At the end of the 6-month period of the study, all children in need of any dental treatment will be referred to a pedodontist in the outpatient clinic. Participants who will be lost to follow-up or who choose to withdraw from the study will be noted and their reasons for doing so as well as the group to which they were allocated will be recorded and reported in the study results*.* All attempts will be made to collect data for the study outcome measures for participants who discontinue or deviate from the interventions.

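### The sole motivational interviewing provider also takes consent from every parent, which conflicts with the promised separation of enrolment from delivery and lets the next MI yes/no status be guessed better than chance

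*Protocol article*

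**What the plan says.** Four places in the protocol article bear on this.

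- **Randomization and allocation concealment** gives enrolment, the random sequence and allocation to one independent person, described as someone "who will be different from the researcher implementing the experimental conditions and assessing the outcomes". Sealed opaque envelopes, put in order by an assistant outside the study, are opened after the child's baseline examination.
- **Ethics approval and consent to participate** gives consent to another person: "A signed informed consent will be obtained by the principal investigator". This applies to all parents, and bracketed initials follow the role.
- **Identifying candidate components**, under motivational interviewing, names the provider: "A single 30–45-min MI session will be offered by one researcher (MI) experienced in motivational interviewing for promoting oral health care".
- **Randomization and allocation concealment** describes the block in two ways. The first is "using a permuted block of size 16, to be able to balance the sample size across the randomization groups". The second, in the next sentence, is "Each block will be a list of 8 randomly ordered conditions". It names no stratification factor.

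The eligibility criteria are set out for the feasibility pilot study and carried over to the factorial trial. They include the parent's willingness to participate.

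**The concern.** The consent conversation settles whether a willing parent enters the trial. If the MI provider holds it, the person with the most direct knowledge of earlier MI assignments takes part in deciding who comes next. Sealed envelopes hide the list, but they do not stop anyone inferring what remains in a block from what has already been used.

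The MI provider could then encourage, delay or discourage a parent according to the assignment that seems due, without intending to. Families with and without MI could come to differ in motivation, and parental motivation plausibly drives both brushing and plaque. The MI main effect decides whether MI enters the optimised package (Selecting the most efficacious components), so a selection effect on that factor would bear on the trial's main decision.

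**Working it through.** **Who does what.** The bracketed letters after the MI provider and after the principal investigator are the same. They could be mistaken for the abbreviation of motivational interviewing. However, the same letters head lists of researchers in the section on candidate components and again among the data analysts in the randomisation paragraph, so they are best read as a person's initials. On that reading one person delivers every MI session and takes every consent.

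**Order of events.** The article does not state for the factorial trial whether consent precedes the opening of the envelope. The envelope is opened after the baseline examination, and consent covers the data to be collected, so consent first is the natural reading.

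**Predictability.** The article gives no figure for this, so there is none to reproduce. The inputs are:

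- 160 parents (Sample size calculation).
- 8 conditions, of which 4 include MI (Table 2).
- Blocks of 16 (8 MI-yes, 8 MI-no) or of 8 (4 and 4), because the text supports either.
- Assumption: at each consent the provider knows every earlier MI assignment and where blocks begin and end.

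For a block of 2m with m MI-yes and m MI-no, a guesser who always names the status with more places left has:

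- expected correct guesses per block = m + (2^(2m) / C(2m, m) − 1) / 2
- expected assignments known with certainty per block = 2m / (m + 1)

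Blocks of 8 (m = 4):

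- Correct: 4 + (256/70 − 1)/2 = 5.33 of 8, or 66.6%. Over 20 blocks this is about 107 of 160.
- Certain: 8/5 = 1.6 of 8, or 20%. Over 20 blocks this is 32 of 160.

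Blocks of 16 (m = 8):

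- Correct: 8 + (65536/12870 − 1)/2 = 10.05 of 16, or 62.8%. Over 10 blocks this is about 100 of 160.
- Certain: 16/9 = 1.78 of 16, or 11.1%. Over 10 blocks this is about 18 of 160.

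Simulation agrees with both closed forms.

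**Range over the main assumption.** The article does not say how soon the MI session follows allocation. The table shows simulated results if the provider's knowledge lags behind by an assumed number of parents.

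| Lag (parents) | Blocks of 16: certain / correct | Blocks of 8: certain / correct |
|---|---|---|
| 0 | 11% / 63% | 20% / 67% |
| 1 | about 5% / 60% | about 8% / 60% |
| 2 | about 2% / 58% | about 2% / 58% |
| 3 | below 1% / 57% | below 1% / 55% |

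**Effect of each remedy.** If the consent-taker does not know past assignments, the best guess is right 50% of the time and nothing is certain. If the MI provider still takes consent but block sizes vary at random among 8, 16 and 24, certainty falls to about 2% while about 62% of guesses are still right.

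**The case against.** A fair opponent would make five points.

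- **Enrolment is not consent.** The randomisation paragraph separates enrolment from delivery, and the ethics section may assign only the signature. This stands in part: the conflict depends on consent being part of entry. The willingness criterion makes that the better reading, but the article does not spell it out.
- **The figures are a best case for the guesser.** This stands. In a clinic that sees hundreds of patients a day, parents may be consented before earlier ones have had their session, and the lag table shows how quickly certainty then disappears. The figures without lag are upper bounds.
- **No strata named does not mean no strata.** The article condenses a fuller protocol that is not shown. This stands as a caveat on the calculation. It does not affect the conflict over who takes consent.
- **Other features limit the harm.** A blinded examiner scores plaque, the outcome is change from the child's own baseline, and the model adjusts for parental education and for brushing with fluoridated toothpaste. These help, but none measures motivation directly, so they would correct selection on it only partly.
- **Varying the block size barely helps.** This stands for guessing: 62% against 63% for blocks of 16. It is a secondary safeguard at most.

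A reader might also infer that the next MI assignment is simply known at consent, or that the MI effect will be biased. The document supports neither. Most assignments remain uncertain even under the upper bound, the provider is not said to have access to the list, and nothing shows that entry would be influenced.

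**Conclusion.** The concern holds as a conflict about roles with a real but bounded risk. Enrolment is promised to be separate from delivery, yet the sole MI provider takes consent from each parent. As upper bounds, that person could be certain of the next MI status for about 11% of parents (blocks of 16) or 20% (blocks of 8), and could guess it correctly 63% or 67% of the time against 50% by chance.

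This rests on four assumptions: the matching initials denote one person; consent precedes the opening of the envelope; the provider tracks earlier assignments and block boundaries without delay; and there are no strata. The calculation covers MI yes/no only, not the full eight-way condition.

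The size of any bias in the MI main effect cannot be derived from the document, and the sample size is unaffected. The point should be corrected before recruitment because the correction is cheap and protects the comparison that decides whether MI is kept.

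**What to change.** 1. **Consent (main remedy).** Change the ethics section so that consent is taken by an existing team member who delivers no component and knows neither the sequence nor past assignments. The blinded plaque examiner is one option, since that person already sees each child at baseline before the envelope is opened. State that consent precedes opening, and that the MI provider meets a parent only afterwards. This costs some minutes per parent for the new consent-taker, with no added staff, visits or participants.
2. **Block description.** Reconcile the two statements in the randomisation paragraph: a block of 16, or a list of 8 conditions. This is a wording change, plus a check that the generated list matches it.
3. **Optional safeguard.** Use randomly varying block sizes in multiples of 8, not disclosed to anyone who recruits or delivers. This needs a new computer-generated list. With blocks of up to 24, each condition can appear three times in a block, so groups could end up to three apart if recruitment stops inside one. A list built to total 160 avoids that. This step should not replace the first, because on its own it removes most of the certainty but little of the guessing.
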